## Abstract

**Background:**

Weight loss is a cornerstone of obesity treatment and diabetes mellitus type 2 (T2D) prevention, but its implementation in clinical practice is limited by its perceived burden and variability in response. Personalizing interventions to increase their success rate is an unmet clinical need.

**Objective:**

Identification of predictive factors associated with successful weight loss after sequential exercise in women with obesity.

**Methods:**

The study will consist of a 2-stage analytical approach, including a predictive validation study and a 2:1 randomized cross-over controlled trial. Women aged 25-45 years with obesity (BMI>30) will be included in the study. The intervention will consist of a progressive protocol of aerobic exercise on a treadmill and a bicycle ergometer. We will measure weight loss in terms of fat mass (FM) and fat-free mass (FFM), metabolic flexibility (MetFlex) as ΔRQ (change in respiratory quotient (VCO2/VO2) between basal and insulin-stimulated state during glucose clamp), insulin sensitivity, glucose tolerance, hemoglobin A_1c_, microbiome composition, and metabolomic signatures.

**Results:**

Recruitment for the trial began in January 2024. A total of 12 participants were enrolled and randomized. Among them 6 participants have completed the first phase of the A-arm and 6 participants have completed the control period of the B-arm and their intervention is ongoing. Recruitment is ongoing. We expect the preliminary data from this study to be completed in 2026.

**Conclusions:**

This intervention will investigate whether whole body and gut MetFlex can be further explored and used as ex ante predictors of successful weight loss following exercise intervention, providing proof of concept and paving the way for personalized lifestyle interventions.

**Trial Registration:**

ClinicalTrials.gov NCT06329349; https://clinicaltrials.gov/study/NCT06329349

**International Registered Report Identifier (IRRID):**

DERR1-10.2196/67570

## Introduction

Obesity has reached pandemic proportions and is a major risk factor for type 2 diabetes (T2D), cardiovascular disease, and other metabolic disorders. Prevention progression to T2D in individuals with obesity through effective lifestyle interventions is a public health priority Substantial and sustained weight loss achieved through lifestyle modifications is a key strategy to reduce the risk of T2D and improve metabolic health [1,2]. The most effective lifestyle interventions aim to achieve a negative net energy balance through two key principles: increasing physical activity and reducing caloric intake. The health benefits associated with regular physical activity are closely linked to the systemic adaptive responses elicited by each training session [3]. Similarly, the beneficial effects of weight loss induced by hypocaloric diets depend on complex adipose tissue remodeling [4]. However, detailed analysis of clinical trial data reveals substantial interindividual variability in responses to these interventions, leading to differences in their effectiveness and health benefits [5,6].

This highlights the need for more personalized lifestyle interventions tailored to individual phenotypes. Recent studies have emphasized phenotype-based interventions as a promising strategy [7,8], particularly focusing on behavioral phenotypes and maladaptive eating patterns in patients with obesity. However, the physiological determinants that may influence weight loss success remain underexplored.

Among the influential determinants that affect the effectiveness and health outcomes of an intervention is an individual’s level of metabolic flexibility (MetFlex). MetFlex refers to the body's ability to adapt in response to changes in metabolic demands and nutrient availability [9]. Impaired MetFlex is a hallmark of obesity and T2D but can be improved by lifestyle interventions such as exercise training or caloric restriction [9-11], similar to improvements in insulin sensitivity. Despite this, MetFlex has not been systematically investigated as a potential mechanism underlying successful weight loss. Impaired MetFlex, that is the limited ability of cells or tissues to cope with excess or deficiency of energy substrates, leads to impaired mitochondrial function and excessive lipid accumulation in ectopic tissues, resulting in metabolic disorders such as T2D or metabolic syndrome.

Another potential predictor of an individual’s ability to respond to lifestyle interventions is the gut microbiota (gut microbiome and metabolome [MIME]). It has repeatedly been shown to be one of the most important sources of interindividual variability in the development of obesity [12] and also responsiveness to weight loss interventions [13]. The microbiome not only influences host physiology directly, for example through contact with immune cells, but also through the large number of metabolites produced, that is, the microbiota-derived metabolome [14]. The composition of the gut microbiota and the microbiota-derived metabolome is largely determined by the host’s diet, which is the main source of nutrients and energy for the microbiota [15]. It is therefore striking that published studies to date have yielded rather inconsistent results regarding dietary interventions to alter gut microbiota composition [16]. This discrepancy can be explained by the large variability of individual microbiomes at the start of the intervention, and also by the fact that the baseline MIME signature is a significant determinant of weight loss success.

Here we propose a comprehensive project MEPHISTO (MEtabolic flexibility to Predict Health lIfeSTyle intervention Outcomes) to investigate whether whole-body and gut MetFlex can be further explored and used as ex ante predictors of successful weight loss following exercise intervention. By identifying key physiological and microbial signatures, this research aims to provide a basis for personalized obesity treatment strategies, ultimately improving diabetes prevention efforts.

## Methods

### Design

A randomized, cross-over, controlled clinical trial will be conducted at Charles University in Prague, Czech Republic. The study will consist of a two-stage analytical approach that will be used to obtain specific results:

1. The first stage is a predictive validation study where we will compare changes in fat mass (FM)/ fat-free mass (FFM) weight loss (after an intervention - predictor variable) with baseline characteristics (independent variable) in the whole sample (n=40). The expected results are the identification of baseline characteristics associated with total and FM/FFM weight loss after the intervention.

2. The second phase is a 2:1 randomized cross-over control trial where we will investigate the effects of the progressive aerobic exercise intervention protocol on MetFlex, metabolic adaptation, and insulin sensitivity. As an exploratory outcome, the fecal metabolomic response will be analyzed.

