### Allocation

After screening for eligibility, a baseline clinical examination will be performed to assess the inclusion and exclusion criteria and to ensure weight stability for 12 weeks before enrollment. Participants will then be randomized by an independent investigator to either exercise intervention arm A or exercise intervention and control arm B using a computer-generated random number table.

After the baseline visit 1 examination, the A-arm will undergo 12 weeks of a progressive aerobic exercise intervention protocol, after which the clinical examination will be repeated. Participants in the B-arm will be assessed after 12 weeks of no intervention and then crossed over to the exercise intervention, after which the final clinical assessment will be carried out (Figure 1).

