### Primary Outcome Measures

Stage 1: the relationship between FM/FFM weight loss and baseline characteristics of MetFlex, calculated as the change in respiratory quotient (ΔRQ).

Stage 2: change in MetFlex, defined as the ΔRQ between basal and insulin-stimulated state during glucose clamp examination, and change in insulin sensitivity (glucose infusion rate).

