### Data Analysis and Statistical Considerations

To assess the effectiveness of the weight loss intervention and identify key predictors of response, such as microbiome, metabolomic profiles, and demographics, we will use generalized mixed effects models. These models account for both fixed effects (the intervention and relevant covariates) and individual variability, providing a robust analysis of the impact of the intervention. In addition, we will develop elastic net-based predictive models, complemented by machine learning algorithms, to stratify individuals into intervention groups, with the secondary aim of identifying responders. These models will be subjected to rigorous validation, including cross-validation or bootstrapping, to ensure their accuracy and generalizability. This approach aims not only to determine the efficacy of the intervention but also to improve personalized treatment by accurately classifying individuals based on their unique profiles, thereby advancing the field of personalized medicine. The analyses will be performed using IBM SPSS Statistics and R statistical packages.

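### Stage 1 is specified and powered as an association within exercised women, which does not support its claims about predictors of exercise success and responders

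*Protocol article*

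**What the plan says.** The Design section describes two stages. Stage 1 relates baseline characteristics to weight and body-composition change after exercise in all 40 women, with the expected output "identification of baseline characteristics associated with total and FM/FFM weight loss after the intervention". Primary Outcome Measures repeats this: "Stage 1: the relationship between FM/FFM weight loss and baseline characteristics of MetFlex". Sample Size gives the inputs for one slope: ΔRQ SD 0.04, weight loss 4 kg (SD 5), a 4 kg difference at a ΔRQ difference of 0.07, 30 women, 80% power, α 0.05.

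The randomised comparison belongs to Stage 2: "The second phase is a 2:1 randomized cross-over control trial", which examines "effects of the progressive aerobic exercise intervention protocol on MetFlex, metabolic adaptation, and insulin sensitivity". Weight loss and its predictors are not on that list. Under Allocation, arm B has 12 weeks without intervention, is assessed, and then crosses over to exercise.

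The claims are wider. The abstract's Conclusions, like the end of the Introduction, asks whether MetFlex can be "used as ex ante predictors of successful weight loss following exercise intervention". Data Analysis and Statistical Considerations names mixed models with the intervention and covariates as fixed effects. It then names elastic net models "to stratify individuals into intervention groups, with the secondary aim of identifying responders", with personalised treatment as the goal.

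**The concern.** A slope of weight change on ΔRQ among women who all exercise has two possible explanations. ΔRQ may mark who responds to exercise, or it may mark whose weight would have moved that way over 12 weeks in any case. Only a comparison of the slope with and without exercise separates them. The trial has a randomised period without exercise, but the article gives it no stated role in the predictor question.

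At stake is the headline reading. A significant Stage 1 slope could be reported as ΔRQ predicting the success of exercise, and women could be labelled responders partly on ordinary 12-week fluctuation. Personalising treatment needs the first explanation; Stage 1 alone supports only an association.

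**Working it through.** **1. Reproduce the stated power.** Inputs are from Sample Size; two-sided α is assumed because sidedness is not stated.

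- Slope = 4 / 0.07 = 57.1 kg per unit ΔRQ.
- Standardised slope r = 57.1 × 0.04 / 5 = 0.457, so R² = 0.209.
- f² = 0.209 / (1 − 0.209) = 0.264.
- Non-centrality at N = 30: √(30 × 0.264) = 2.815.
- Power by z: Φ(2.815 − 1.96) = 80.4%. By non-central t with 28 df: 77.6%.

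A two-group comparison of 4 kg with SD 5 does not reproduce the figure (59% at 15:15, 54% at 20:10). The stated 80% is therefore the power of a slope under one condition, with no control term.

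**2. Can Stage 1 tell the two explanations apart?** Simulation of 10,000 trials, 30 women at 20:10, with slope 57.1 in both exercise and control periods. The residual SD is 5 × √(1 − 0.209) = 4.45 kg in both; using it for control is an assumption. ΔRQ then has no relation to the response to exercise.

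- Stage 1 slope significant: 74% of trials.
- ΔRQ-by-condition test, first period, significant: 5% of trials, the nominal level.

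The Stage 1 test is positive about as often as when ΔRQ truly predicts exercise response, so a positive result does not favour either explanation.

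**3. Does the intervention main effect help?** With main effects only, the mixed model has one common ΔRQ slope and a shift in mean between conditions. The question is whether the slope differs between conditions, and that is the product term, which is not stated.

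**4. How precise would the product term be?** Take 30 exercise and 10 control periods, treated as independent, with true control slope zero. The control residual SD is not in the documents; 2 to 5 kg is shown.

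- Exercise slope SE = 4.45 / (0.04 × √28) = 21.0.
- Control slope SE = SD / (0.04 × √8) = 17.7 (SD 2) to 44.2 (SD 5).
- SE of the difference = √(21.0² + 17.7²) = 27.5, to √(21.0² + 44.2²) = 48.9.
- Power for a difference of 57.1 = Φ(57.1/27.5 − 1.96) = 55%, down to Φ(57.1/48.9 − 1.96) = 21%.
- Half-width of the 95% interval = 1.96 × 27.5 = 54, to 1.96 × 48.9 = 96 kg per unit ΔRQ.

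If the control slope were half the exercise slope, power in the randomised first period (20:10) would be only 15% to 9%. With equal residual SDs, 80% power for the interaction at 2:1 would need about 135 women.

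**The case against.** The best defence has four parts.

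- *The Stage 1 text is modest.* The Design section promises only an association, and the abstract speaks of proof of concept. Forecasting who loses weight on a programme is a legitimate prognostic question. This stands, and it is why the Stage 1 regression should be kept. It does not cover the wording on responders and personalisation.
- *Control data may enter the mixed model.* An intervention fixed effect would have nothing to contrast if only exercise periods were modelled. This also stands: a reader might infer that the plan ignores the control period altogether, and the text does not establish that. But a main effect does not answer the question. An analysis plan not shown may contain an interaction; even so, the article itself fixes Stage 1's outcome, analysis set and power as a single-condition association.
- *Background change is limited.* Weight stability for 12 weeks before enrolment is required, and Major Confounders provides for monitoring intake and activity. These measures reduce weight change unrelated to exercise but do not remove it.
- *The interaction is underpowered.* True, and so it should not act as a gate: a null result would be likely even if ΔRQ did predict exercise response.

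Two stronger readings are tempting. From "After the baseline visit 1 examination" a reader might infer that arm B's predictor is 12 weeks old when exercise starts and that its weight change spans the control period. The article does not say so. That clause introduces arm A's schedule, and the same paragraph gives arm B an assessment just before crossover. A reader might also infer that if weight varied as much without exercise as with it, there would be no responders. Zero variance in response would mean that all women respond alike, not that none responds.

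**Conclusion.** The point holds as a mismatch between analysis and claim. Stage 1 as specified supports the statement that baseline ΔRQ is associated with weight change during the exercise programme. It does not support calling ΔRQ a predictor of exercise response or labelling women as responders to exercise. No stated number is wrong on this account; the 80% reproduces for the narrower question.

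The size is shown by the equal-slopes case: Stage 1 is significant in about 74% of trials although ΔRQ has no bearing on response. That figure rests on the planned slope and on the same residual SD in both conditions. The power of 21% to 55% for the interaction rests on a zero control slope, an assumed control SD of 2 to 5 kg, and independence of arm B's two periods. The stratification wording is a smaller matter: only one intervention is given, and arms are assigned at random, so there are no intervention groups to stratify women into.

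**What to change.** 1. Keep the Stage 1 regression as the primary association.
2. Add to the mixed model a ΔRQ × condition term (exercise versus control), with period and a random effect for woman. Use the first 12 weeks of both arms and arm B's exercise period, and state that arm B's post-control assessment is the baseline for its exercise period.
3. Report the control-period slope and the interaction with 95% confidence intervals, as estimates and not as a pass/fail gate.
4. Word Stage 1 conclusions and any responder label as association with weight change during the exercise programme, unless the interaction supports more.
5. Remove the phrase on stratifying individuals into intervention groups.

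Cost: analysis and wording only. No extra visit is needed, since arm B is already assessed before and after its control period; the article does not itemise that assessment, but Stage 2's outcomes require ΔRQ at both ends. Results reports 12 women randomised and recruitment continuing, so the term can still be prespecified. The price is a wide interval and a more modest headline claim.

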### Participants

Women aged 25-45 years with obesity (BMI>30) are included in the study. Only female participants were selected to reduce heterogeneity, as MetFlex and energy metabolism are sex-dependent and to improve statistical power in a small sample. This selection aligns with previous studies at our research center and will allow for future data pooling. Practical considerations, including shared facilities and standardized protocols, also supported this decision.

### Inclusion and Exclusion Criteria

The inclusion and exclusion criteria are mentioned in Textbox 1.

Inclusion and exclusion criteria.
**Inclusion criteria**
Participants who meet the following criteria will be eligible for the study:• BMI>30• Age 25-45 years
**Exclusion criteria**
• Active cancer• Diabetes (medical history, fasting glycemia >7.6, and glycemia of >11.1 on the 2-hour oral glucose tolerance test)• Uncontrolled endocrine diseases• Corticosteroid therapy• Immune-suppressive therapy• Pregnancy• Breastfeeding

### Recruitment Process

Potential volunteers will be recruited from outpatients and previous research participants at the Department of Internal Medicine, University Hospital Kralovské Vinohrady, Prague, or through social media advertising via the university and hospital platforms. Our research participant network is only used to advertise studies, and individuals who have previously participated in interventional trials will not be included. In addition, patients from the Obesitology Centre will be considered only before their enrollment in clinical interventional programs to prevent previous interventions from influencing study outcomes.

### Allocation

After screening for eligibility, a baseline clinical examination will be performed to assess the inclusion and exclusion criteria and to ensure weight stability for 12 weeks before enrollment. Participants will then be randomized by an independent investigator to either exercise intervention arm A or exercise intervention and control arm B using a computer-generated random number table.

After the baseline visit 1 examination, the A-arm will undergo 12 weeks of a progressive aerobic exercise intervention protocol, after which the clinical examination will be repeated. Participants in the B-arm will be assessed after 12 weeks of no intervention and then crossed over to the exercise intervention, after which the final clinical assessment will be carried out (Figure 1).

**Figure 1 figure1:**
[figure not shown]
Enrollment, intervention, and evaluation project schedule.

### Intervention

The exercise intervention is designed according to the 2021 European Association for the Study of Obesity (EASO) guidelines to maximize the effect of reducing body weight and adipose tissue [17]. These guidelines recommend 150 to 200 minutes of at least moderate-intensity aerobic exercise (Grade A). The exercise intervention will last 12 weeks, during which the study participants will perform aerobic endurance exercise 3 times a week in groups of 6 people under supervision.

The exercise will be performed as fast walking on a treadmill. The duration and intensity of the exercise will be controlled so that the energy expenditure per unit of exercise is 150 kcal in the first week, increasing by 50 kcal each week thereafter until week 6 when it reaches 400 kcal, a level that will be maintained until the end of the intervention [18]. The walking pace will be adjusted individually, based on input of indirect calorimetry, to correspond to moderate intensity physical activity (metabolic equivalent of task 3 to 6) and to achieve the required energy expenditure in the given time. A progressive increase in energy expenditure during the intervention will be therefore ensured by an appropriate combination of increasing intensity and duration of exercise. For this reason, the duration of each session will be individual, for example, 30 minutes of walking at a speed of 5 km/hour corresponds to approximately 180 kcal for a person weighing 95 kg [19].

During the intervention, participants’ compliance will be strictly monitored: if a session is missed, it will be made up as soon as possible. If more than one session is missed (eg, due to illness), the intervention will be extended to make up for the missed sessions, but not more than 2 weeks. Only participants who complete at least 90% of the training sessions will be included in the analysis (so they can skip a maximum of 3 sessions).

### Primary Outcome Measures

Stage 1: the relationship between FM/FFM weight loss and baseline characteristics of MetFlex, calculated as the change in respiratory quotient (ΔRQ).

Stage 2: change in MetFlex, defined as the ΔRQ between basal and insulin-stimulated state during glucose clamp examination, and change in insulin sensitivity (glucose infusion rate).

### Secondary Outcome Measures

Changes in glucose tolerance (glucose level on the 2-hour oral glucose tolerance test), hemoglobin A_1c_, and insulin sensitivity (glucose infusion rate) following the intervention will be evaluated following the intervention.

### Exploratory Outcome Measures

Changes in microbiome composition and metabolomic signatures will also be assessed following the intervention.

### Data Collection

#### Anthropometry

The anthropometric measures used were weight, height, bioimpedance analysis (TANITA MC-980U Plus Multi-Frequency Segmental Body Composition Analyzer, manufacturer, state), DXA (Hologic’s Horizon DXA Platform), and plethysmography (BOD POD’s Air Displacement Plethysmography Cosmed).

#### Indirect Calorimetry

The resting gas exchange will be measured using a canopy hood ventilated system with a metabolic cart (Quark RMR, Cosmed). Standard air, gas, and flow calibrations will be performed before each measurement. Important deviations may limit the reliability of measurements, to correct for this postcalorimetric simulation with high-precision mass flow regulators (EL-Flow Prestige, Bronkhorst high-tech B.V., NL) will be done after each measurement with a defined gas mixture. VO_2_, VCO_2,_ and nitrogen loss per 24 hours will be used to calculate basal substrate utilization of carbohydrates, fat, and protein.

